**3.5.1. Description of the tests**

Respiratory and non-respiratory specimens, naturally contaminated, will be collected in disposable receptacle. The specimens should be given to the laboratory up to 24 hours after being collected and will be submitted to bacilloscopy after the Ziehl-Neelsen coloration. After being processed by the Kubica method, they will be cultivated by the BACTEC MGIT 960 method and in Löwenstein-Jensen in Rio de Janeiro and in Vitoria, and by the BACTEC MGIT 960 method. Cultures contaminated by other microorganisms will be called as contaminated and considered as negative for calculation in statistical tests. In the clinical specimens of the included patients, the sensitivity test will be carried out by the gold pattern tests and by BACTEC MGIT 960. Additionally, the positive cultures will be appraised as for the sensitivity of *M. tuberculosis* for isoniazid, rifampicin, streptomycin and ethambutol by the indirect test of proportions (one strain/patient).

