**3.6. Randomization - Clinical procedures for Open Clinical Trial Practice**

The physician that routinely evaluates the patients under active TB suspicion, invited to voluntarily participate of the study, once deciding the patient's inclusion in the protocol will request an envelope that contains in its external side four key questions: a) which is the patient's probability to present TB (high/intermediary or low); b) the choice above was based in the results of radiological examination; c) in his/her opinion, should the patient begin anti-TB treatment (yes or not) d) what is the patient's risk of having resistant TB (high/intermediary or low). The four questions filled out, the doctor will open the envelope and inside it he/she will identify which is the diagnostic method that should be requested for the patient. The envelopes will be numbered in growing order and the indication of the diagnostic tests inside them has been previously randomized by a professional non-participant of the study. This procedure **attempts to guarantee the concealing of the randomization and at the same time it will be possible to check the success of the randomization**.

In the routine investigation of patients under TB suspicion, the following information is collected in standardized forms: a) socio-demographic data; b) organs and human body systems examination; c) exposure to TB, disease and treatment history; d) past pathological history; e) physical exam; f) chest X-ray result; g) tuberculin skin test result; h) HIV test result.

Respiratory specimens include spontaneous sputum, induced sputum and bronchoalveolar wash. Non-respiratory specimens include biopsy material and synovial, pleural, CSF liquids, etc. A minimum of two and a maximum of three specimens per patient will be appraised in this study. Clinical specimens will not be collected out of the TB diagnostic investigation routine in the hospital.

Following the routine, the clinical samples will be forwarded to the mycobacteriology laboratories in the next working day. Only in the clinical samples of patients that have received randomization for the MGIT, should the laboratory personnel be informed that the MGIT must be performed.

To analyze the outcome of the study, the key information below, present in the medical handbooks or routine record cards of the TB Program, will be copied to the study’s own forms.

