**OUTCOMES, INDICATORS AND RESPONSIBLE FOR THE DATA COLLECTION**

| Outcome | Indicator | Responsible for the information collection |
| --- | --- | --- |
| 1. Time in hospital | PCTH Record card | Nurse |
| 2. Number of deaths | Related toTB  Black book, PCTH-Amb Record card, Medical handbook  Related to non-TB  HUCFF’s Medical handbook | Nurse |
| 3. Result of the treatment  (cure, abandonment, treatment failure, change of diagnosis) | Black book , PCTH Record card – Ambulatory | [name] |
| 4. N general adverse effects related to drugs | Medical handbook | Physician |
| 5. N adverse effects related to anti-TB drugs | Medical handbook, PCTH Record card | Physician |
| 6. N adverse effects related to the use of diagnostic methods (i.e.: bronchoscopy, biopsy, induced sputum, etc) | Medical handbook | Physician |
| 7. Time of the diagnosis (in days)  From the randomization to the result release by the Lab | Book of the laboratory - or electronic data in Medtrek | Nurse |
| 8. Time of sensitivity Test | Lab Book / Medtrek | Nurse |
| 9. Time of anti-TB schedule change | PCTH Record card at the end of the 2^nd^ month  PCTH Record card at the end of 6^th^ month | Nurse |
| 10. Proportion of patients with false negative bacteriological result | Medical consultation at the end of the 2^nd^ month | Physician |
| 11. Clinical Worsening | Medical handbook / PCTH Record card 7, 15 30, 60, 180 days | Physician |
| 12. Radiological Worsening | 60 days | Physician |
| 13. Time of symptoms and beginning of the anti-TB treatment | Medical handbook / PCTH  PCTH Record card - Ambulatory and Active Search | Nurse |
| 14. N processed materials until the TB diagnosis | Card registry of the laboratory | Nurse |
| 15. N processed materials after the TB diagnosis | Card registry of the laboratory | Nurse |
| 16. Proportion of patients that develop resistant TB | Laboratory Book - PCTH Record card | Nurse |
| 17. Proportion of bacteriological conversion at the end of the 2^nd^ month | Laboratory Book , Medical Handbook, PCTH Record card | Nurse |

Other information, necessary to analyze the outcomes related to the cost- effectiveness analysis that are not available in the medical handbooks or routine record cards of the Hospital Program will be collected in a standardized way (in annex) by a professional trained at SIA-SUS and in other database of the Ministry of Health and Ministry of Education.

Study forms

- Forms of free and clear consent and of inclusion

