**3.8. Definition of a TB Suspect Case, Active TB Case and Discordance Analysis**

**Pulmonary and /or pleural pulmonary form**

Every patient under pulmonary TB suspicion that presents respiratory signs/symptoms and with alterations in the chest X-ray will be classified in three groups;

a) Typical pattern of TB: infiltrated in upper third (LS or apical seg of LI), with or without cavity; bilateral miliar infiltration; unilateral pleural hemorrhage with upper lobe infiltration .

b) Intermediate pattern of TB: infiltrated in middle or lower third, with or without cavity in these areas; isolated pleural hemorrhage, infiltrated in upper thirds of undetermined activity; diffuse abnormalities (not miliar); mediastinal or hilar enlargement .

c) Atypical Pattern of active TB: multifocal hypotransparency images; alveolar hypotransparency images; calcified nodules.

“**Confirmed TB case"** will be defined as the patient with at least one positive culture for *M. tuberculosis* in L-J or MGIT960*.*

**“Probable TB case"** will be defined as the patient that presents negative results to culture with one or more of the following characteristics:

a) clinical answer to the treatment (defined as improvement to X-ray, b) decrease of the cough and 3% weight gain in relation to the beginning of the treatment) and absence of alternative diagnosis;

Patient not classified as confirmed case or probable TB will be considered "non- TB."

**Treatment failure:** patient that remains with positive bacteriological test (two samples in a 30 day interval) after 5 months of treatment, standardized by MH

High risk factors for resistant TB:

a) Relapsing TB (previous complete treatment for TB with apparent cure), b) Treatment failure (patient under treatment ≥ 4 months with positive bacilloscopy), c) Patient’s contact with multidrug resistant-TB.

3.9 **Main outcome**  The primary outcome was defined as the proportion of patients in each group whose initial prescription changed by the second month after randomization. The ‘change’ could be initiating or stopping TB treatment.

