**Secondary outcomes-**

-The secondary outcomes were the mean time to changing the initial clinical prescription,

-The proportion of patients with positive culture and positive smear microscopy for TB,

-The proportion of patients initiating treatment before test results,

-The occurrence of severe adverse events

-Patient satisfaction with the overall treatment- Number of deaths by any cause in the patients included in the study.

- Proportion of patients with TB diagnosis sensitive or resistant to anti-TB medicines (RIF, INH, SM and EMB), with the methods employed in the study.

- Proportion of patients that undergo anti-TB treatment failure during the therapy.

- Proportion of drug resistant TB development in the patients that used the different diagnostic methods and that were classified as treatment failures.

- Proportion of bacteriological conversion (bacilloscopy and culture for mycobacterium) due to the anti-TB treatment at the end of the second and sixth month of anti-TB treatment.

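### Contaminated follow-up cultures are scored as negative, so an unreadable culture can support conversion and cannot support treatment failure

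*Protocol*

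**What the plan says.** Protocol section 3.5.1 sets one scoring rule: "Cultures contaminated by other microorganisms will be called as contaminated and considered as negative for calculation in statistical tests". It is not restricted to the diagnostic culture, to a specimen type or to an outcome. Nowhere else does the protocol give a repeat-culture rule, a not-evaluable category or a separate rule for follow-up cultures.

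Several outcomes and definitions depend on culture:

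- Conversion is a secondary outcome: "Proportion of bacteriological conversion (bacilloscopy and culture for mycobacterium) due to the anti-TB treatment at the end of the second and sixth month" of treatment.
- Treatment failure is a secondary outcome: "Proportion of patients that undergo anti-TB treatment failure during the therapy". Section 3.8 defines it as a "patient that remains with positive bacteriological test (two samples in a 30 day interval) after 5 months of treatment".
- The outcomes table that follows the randomization section lists "Proportion of patients with false negative bacteriological result" as item 10.
- A probable TB case (section 3.8) "will be defined as the patient that presents negative results to culture with one or more of the following characteristics", the characteristic being clinical response without an alternative diagnosis.

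On the number of specimens, the randomization section says of the diagnostic work-up: "A minimum of two and a maximum of three specimens per patient will be appraised in this study". Section 3.7 asks for two sputum specimens, for smear and culture, at the monthly evaluations.

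**The concern.** A contaminated culture carries no information on whether *M. tuberculosis* is present. Scoring it as negative is harmless only where negative means that no positive result was obtained. That is the meaning for baseline yield, where all randomised patients form the denominator and the question is how many had a positive culture.

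For conversion and failure, negative means that the bacilli have gone. The same rule then credits treatment with a success that nobody observed. At stake is the accuracy of the reported conversion and failure rates. Both err in the favourable direction, by an amount that grows with contamination.

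**Working it through.** The protocol states no figure for contamination, conversion or failure, so there is no planned number to reproduce. What follows shows how the rule behaves on assumed values.

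**Inputs.** All three are assumptions:
- contamination c = 5%, 10% or 15%, independent of the patient's true status;
- true culture conversion π = 70%, 80% or 90%;
- true failure f = 5% or 10%.

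Only culture is considered. A positive smear would shrink every effect below.

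**Conversion, one specimen decides.** Observed = π(1 − c) + c = π + (1 − π)c.

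| True π | c = 5% | c = 10% | c = 15% |
| --- | --- | --- | --- |
| 70% | 71.5% | 73.0% | 74.5% |
| 80% | 81.0% | 82.0% | 83.0% |
| 90% | 90.5% | 91.0% | 91.5% |

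Example: 0.80 + 0.20 × 0.10 = 0.82.

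**Conversion, two specimens of the same true status, contaminated independently.** A non-converter is misread only if both are contaminated, so observed = 1 − (1 − π)(1 − c²). At π = 80%:
- c = 5%: 80.05%;
- c = 10%: 1 − 0.20 × 0.99 = 80.2%;
- c = 15%: 80.45%.

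**Failure, two positive samples 30 days apart, one culture each.** Both must be readable, so observed = f(1 − c)².
- f = 10%: 9.0%, 8.1% and 7.2% for c = 5%, 10% and 15%.
- f = 5%, c = 10%: 0.05 × 0.81 = 4.05%.

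If two specimens are taken on each occasion and one readable positive is enough, observed = f(1 − c²)². At f = 10% and c = 10% this is 0.10 × 0.99² = 9.8%.

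**With contamination treated as no result.** Under the same independence assumption, the rates among patients with a result return to π and f. The share without a conversion status is c if one specimen decides (10% at c = 10%) and c² with two (1%). The two extreme assignments at π = 80%, c = 10% then give:
- one specimen: 0.80 × 0.90 = 72% (all counted positive) to 82% (all counted negative);
- two specimens: 0.80 × 0.99 = 79.2% to 80.2%.

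The second specimen therefore removes most of the problem, provided the rule says that it may be used. Apart from one positive culture confirming a case at diagnosis, the protocol does not say how a contaminated and a readable culture combine.

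**The case against.** The case for leaving the rule alone has several parts.

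- **Smear and second specimens limit the damage.** Conversion uses smear as well as culture, and failure rests on any positive bacteriological test, so a positive smear still shows non-conversion or failure. Two specimens per evaluation make a patient-level error uncommon. This stands and bounds the effect. It does not make the rule right for a smear-negative patient whose cultures are unreadable.
- **Counting contamination against the test is legitimate in a pragmatic trial.** For yield and for false negatives this stands: a contaminated culture in a patient with TB is a failure of the diagnostic strategy to deliver a diagnosis. The probable-TB class should also keep the rule. Section 3.8 calls anyone who is neither confirmed nor probable non-TB, so if contamination became no result there, a clinical responder with only contaminated cultures would drop to non-TB. The argument does not carry over to conversion and failure, where the rule favours the result.
- **The SAP may handle it.** Sensitivity analyses commonly sit in a SAP, but the scoring rule itself is written in the protocol and can be judged as written.

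A reader might go further and infer that, because the arms differ by culture medium, the rule biases the MGIT versus Löwenstein-Jensen comparison of conversion. The documents do not support that. Allocation of medium is described for specimens from TB suspects. Section 3.7 names no medium for follow-up cultures, and section 3.5.1 can be read as using both media. With assumed contamination of 5% and 10% in the two arms, the spurious difference at 80% true conversion would be 82% − 81% = 1 point if one specimen decides. Neither rate is in the protocol, and with equal rates the difference is zero.

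**Conclusion.** The point holds for bacteriological conversion and treatment failure only. As written, the rule turns an uninterpretable follow-up culture into a favourable result unless a smear or the other specimen is positive.

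The distortion of the absolute rates is modest. On the illustrative values (80% true conversion, 10% contamination independent of true status) it is 2 points if one specimen decides and about 0.2 points if both of two must be contaminated. The size and direction of any between-arm bias cannot be established from the documents.

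The primary outcome, change of initial prescription by the second month, is not scored from culture and is unaffected. Nothing here counts against the rule for baseline yield, false negatives or probable TB. This is a flaw in secondary outcomes that should be corrected because it is written into the protocol and cheap to remove.

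**What to change.** Limit the sentence in section 3.5.1 to baseline diagnostic outcomes, leaving the section 3.8 case definitions as they are. Add that, for culture conversion and treatment failure:

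- a contaminated culture is no result;
- it is resolved from the patient's other specimen at that visit;
- if no readable culture remains, the culture status is missing;
- a sensitivity analysis counts such cultures once as negative and once as positive.

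Report the contamination proportion by arm.

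The cost is a short text change and one extra table. No new data are needed, since contaminated cultures are already labelled as such and section 3.7 already asks for two follow-up specimens. The downside is that a few patients will have a missing conversion or failure status.

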***M*. *tuberculosis* Identification*:***

Conventional methods - The selected strains will be identified as *M. tuberculosis,* based upon the characteristics of the colonies (rough, cream and opaque), in the capability of producing niacin, nitrate reductase and catalase heat inactivation.

**Identification of the *M. tuberculosis* growth by the BACTEC MGIT 960 System** - In the bottom of each tube there is a fluorescence sensor. The fluorescence level that each tube emits corresponds to the amount of oxygen consumed by the organism, which is proportional to the number of bacteria in the tube. When the oxygen is consumed, an oxi-reduction reaction occurs causing the increase of fluorescence. That fluorescence can be detected through a transiluminator with a UV bulb in a 365 nm wavelength. Five hundred microliters of treated sediment of the clinical specimens will be inoculated in each one of the MGIT tubes without and with PNB in a 500g/mL concentration. The result of the *M*. *tuberculosis* growth identification will be defined based on its growth inhibition in the MGIT culture medium containing PNB and the growth (positive) in the MGIT control tube.

*A standardized suspension of the M. tuberculosis, M. bovis, M. africanum strains and of other species of mycobacteria grown in solid medium will be prepared. Five hundred microliters of the suspensions will be inoculated in MGIT 960 medium with 500mg/L of PNB and control medium without PNB. The flasks will be homogenized, identified through bar code reading and placed into the specific shelf-carrier of the BACTEC MGIT 960 instrument. The result of the M. tuberculosis growth identification will be defined based on its growth inhibition in the MGIT culture medium containing PNB and the growth (positive) in the MGIT control tube. The result is given between 5 to 15 days, depending on the bacterial growth.*

**Drug sensitivity test with the BACTEC MGIT 960 System -** The *M. tuberculosis* strains will be subcultivated in MGIT tube until it indicates a positive result in the BACTEC MGIT 960 System. Five tubes of MGIT (7 mL) will be identified and placed in the shelf-carrier (AST Set Carrier) in the following sequence: GC (control - Without drugs), STR (Streptomycin), INH (Isoniazid), RIF (Rifampicin) and EMB (Ethambutol). Then, a volume corresponding to 0,8 mL of BACTEC MGIT SIRE Supplement will be added to each tube. Aseptically, using a micropipette, 100 μl will be pipetted of the stock solution of each drug in the 4 tubes, so as to reach the final concentrations presented in table 1. Starting from the *M. tuberculosis* cultures with growth in the MGIT tubes a 1:100 dilution will be prepared, by the addition of 0,1 mL of the cultures in 10 mL of sterile saline solution. After the homogenization of the bacterial suspensions, 0,5 mL of the diluted suspension (1:100) will be inoculated in a tube of MGIT culture medium (control without drugs). In other the tubes containing the drugs (INH, RMP, EMB and SM) 0,5 mL of the not diluted suspension will be inoculated. The flasks will be homogenized, identified through bar code reading and placed in the shelf-carrier of the sensitivity test in the BACTEC MGIT 960 instrument. The results (sensitivity or resistance to the drugs) shall be defined according to the criteria established by the manufacturer (Becton Dickinson), based on the algorithm of the System computer program.

**Drugs sensitivity test by the method of the proportions -** It will be carried out based on the indirect method described by Canetti, Rist and Grosset (1963). Starting from the bacterial growth in solid medium, without drugs, a suspension will be made, using the largest number of colonies possible, in a 16 x 150mm tube containing about 10 glass pearls and approximately 0,5 mL of sterile distilled water. The tube will be agitated in vortex for 20 to 30 seconds in order to homogenize the suspension. Then it will be slowly dripped into the sterile distilled water suspension until a turbidity is obtained, corresponding to tube number 1 in Mac Farland's scale or to a BCG 1mg/mL standard suspension. From this standardized suspension decimal dilutions will be made until 10^-6^ and 0,1mL will be inoculated in the control tubes without drugs and in the tubes with drugs. After the inoculation, the tubes will be placed horizontally inclined on a tray so that the inoculum is distributed on the whole surface of the medium, keeping them with the lid loose for 24-48 hours in order to dry the inoculum. The tubes will then be incubated in vertical position at 37ºC for 28 days. After this period, the reading of the test and the results interpretation will be accomplished according to the recommendations of the Bacteriological Norms of the Ministry of Health Technical Manual.

In HUCCF-UFRJ Mycobacteriological Laboratory, the several tasks are distributed among the technicians. Thus, a technician is responsible for the daily processing of the clinical specimens through the Kubica method and for inoculation the sediment in Lowenstein-Jensen medium. Another technician is responsible for carrying out the drugs sensitivity tests through the method of proportions, a third one for the inoculation and sensitivity test in the tubes of the BACTEC MGIT 960 method, of its specimens and of other studies, etc. This way, there is no possibility for the technician to be induced to favour the positive reading of one or another method. To this division of tasks is added the fact that the MGIT960 reading is totally automated, the result being printed by the computer of the equipment in thermal impression ribbon, which will be photocopied and filed in a suitable place.

**3.6. Randomization - Clinical procedures for Open Clinical Trial Practice**

The physician that routinely evaluates the patients under active TB suspicion, invited to voluntarily participate of the study, once deciding the patient's inclusion in the protocol will request an envelope that contains in its external side four key questions: a) which is the patient's probability to present TB (high/intermediary or low); b) the choice above was based in the results of radiological examination; c) in his/her opinion, should the patient begin anti-TB treatment (yes or not) d) what is the patient's risk of having resistant TB (high/intermediary or low). The four questions filled out, the doctor will open the envelope and inside it he/she will identify which is the diagnostic method that should be requested for the patient. The envelopes will be numbered in growing order and the indication of the diagnostic tests inside them has been previously randomized by a professional non-participant of the study. This procedure **attempts to guarantee the concealing of the randomization and at the same time it will be possible to check the success of the randomization**.

In the routine investigation of patients under TB suspicion, the following information is collected in standardized forms: a) socio-demographic data; b) organs and human body systems examination; c) exposure to TB, disease and treatment history; d) past pathological history; e) physical exam; f) chest X-ray result; g) tuberculin skin test result; h) HIV test result.

Respiratory specimens include spontaneous sputum, induced sputum and bronchoalveolar wash. Non-respiratory specimens include biopsy material and synovial, pleural, CSF liquids, etc. A minimum of two and a maximum of three specimens per patient will be appraised in this study. Clinical specimens will not be collected out of the TB diagnostic investigation routine in the hospital.

Following the routine, the clinical samples will be forwarded to the mycobacteriology laboratories in the next working day. Only in the clinical samples of patients that have received randomization for the MGIT, should the laboratory personnel be informed that the MGIT must be performed.

To analyze the outcome of the study, the key information below, present in the medical handbooks or routine record cards of the TB Program, will be copied to the study’s own forms.

